#### Secondary outcomes

##### Postoperative recovery of gastrointestinal function

Measured variables for this outcome include: water intake time (the time of first water intake after operation), solid food tolerance time (solid food tolerance indicates that there is no nausea or vomiting within 4 h after a meal), first anal exhaust time, the time at which the patient is able to leave the bed, and the use of gastrointestinal functional adjuvant medicines.

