### Sample size calculations

This study utilizes a superiority design, and the sample size has been calculated according to the primary endpoint of time to first bowel sound recovery following surgery. Based on a single-center preliminary test, this recovery time was 60.320 ± 9.8167 h in sham TEAS-treated individuals and 51.558 ± 17.8499 h in patients who received TEAS during all phases of the perioperative period. Therefore, the difference between the two groups was 8.762 h. Adopting a conservative point of view, the larger standard deviation of 17.8 was used to calculate the optimal sample size. In Part 1, according to a ratio of 3:2 and a power of 90%, a total of 110 and 73 patients were needed per group. To additionally account for a 10% drop-out rate, these case numbers were increased to 120 and 80, respectively. The reason for this unbalanced design between the groups was that both the T1 and T3 groups underwent TEAS before and during the operation, and thus have the potential to achieve a better therapeutic outcome. To ensure maximal possible patient protection, 80 cases were included in the Con and T2 groups, while 120 cases were included in the T1 and T3 groups.

In Part 2, as all patients received the same preoperative and intraoperative interventions, the allocation ratio was altered to 1:1:1:1, with 100 participants per group.

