### Statistical analysis

Continuous variables will be expressed as: mean (SD), median (interquartile range (IQR)), or minimum and maximum. For comparisons between treatment groups, analyses of variance (ANOVAs) will be used for normally distributed variables, and the Kruskal–Wallis *H* test will be used for non-normally distributed variables. Categorical variables will be expressed as numbers (%), and will be analyzed via chi-square tests for between-group comparisons.

Statistical significance for this study is defined as α = 0.05 for a two-sided test. *P* values will be rounded to three decimal places; values below 0.001 will be reported as < 0.001. Statistical analyses will be conducted using SAS version 9.4 (SAS Institute Inc.).

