### Primary/secondary efficacy endpoints

A covariance model (ANCOVA) will be fitted, with primary endpoint changes from baseline serving as the dependent parameter, and with treatment group, baseline, and study site serving as fixed effects for consideration of site–treatment interactions. For ordinal and categorical variables, a Cochran–Mantel–Haenszel (CMH) test will be used, with study site as a stratifying factor.

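### The two analysis sections disagree on how secondary efficacy outcomes are tested, and the continuous ones have no stated test that uses study site

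*Protocol article*

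**What the plan says.** The Statistical analysis section sets general rules for comparing groups. For continuous variables, "analyses of variance (ANOVAs) will be used for normally distributed variables", and Kruskal–Wallis replaces ANOVA when the variable is not normal. Categorical variables "will be analyzed via chi-square tests for between-group comparisons". No site term appears, and the section is not limited to baseline or descriptive tables.

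The Primary/secondary efficacy endpoints section brings in study site twice. The first is an ANCOVA with treatment group, baseline and study site, whose dependent variable is the change from baseline in the primary endpoint. The second covers ordinal and categorical variables, for which a Cochran–Mantel–Haenszel (CMH) "test will be used, with study site as a stratifying factor".

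The continuous secondary outcomes include "water intake time (the time of first water intake after operation), solid food tolerance time", first exhaust and time out of bed (Postoperative recovery of gastrointestinal function), and cumulative analgesic dose (Postoperative pain treatment). The Design section describes five hospitals at four institutions. Under Randomization and blinding, surgical site (gastric or colorectal) is the only stratifying factor named.

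**The concern.** For categorical efficacy outcomes two tests are stated for the same comparison, one ignoring site and one stratified by it, with no rule for choosing. For continuous secondary outcomes the only test explicitly stated leaves site out, although the plan uses site for the primary endpoint and, in one of the two sections, for categorical outcomes.

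Two things are at stake. An analyst could pick either test for a categorical outcome after seeing the data. And if sites differ in outcomes such as first drink, first solid food or mobilisation, those differences stay in the error term and widen the confidence intervals. That such outcomes follow ward routine is plausible, but it is an assumption and not a statement of the article.

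**Working it through.** **1. The two sections side by side.**

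| Outcome type | Statistical analysis | Primary/secondary efficacy endpoints |
|---|---|---|
| Primary endpoint | ANOVA or Kruskal–Wallis, no site | ANCOVA with treatment, baseline, site |
| Continuous secondary | ANOVA or Kruskal–Wallis, no site | nothing explicit |
| Categorical | chi-square, no site | CMH stratified by site |

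The ANCOVA cannot simply be carried over to the continuous secondary outcomes. It models a change from baseline with baseline as a covariate. Times to water, solid food, exhaust and leaving bed, and postoperative analgesic dose, have no baseline value. (The SF-8 score and the blood indexes do have a preoperative value.)

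**2. The plan's own figure.** Inputs from Sample size calculations and Statistical analysis: "the difference between the two groups was 8.762 h"; "the larger standard deviation of 17.8 was used to calculate the optimal sample size"; "Statistical significance for this study is defined as α = 0.05 for a two-sided test"; and "according to a ratio of 3:2 and a power of 90%, a total of 110 and 73 patients were needed per group". With k = 1.5,

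n(smaller) = (1 + 1/k) × [σ(z₀.₉₇₅ + z₀.₉₀)/Δ]² = 1.667 × [17.8 × (1.960 + 1.282)/8.762]² ≈ 72.3, so 73; and 1.5 × 73 = 109.5, so 110.

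The stated 73 and 110 reproduce. This calculation sizes the primary endpoint only. It contains no between-site variance and sets no power target for any secondary outcome.

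**3. Gain from adding site.** Let r be the share of outcome variance lying between sites (assumed; the article gives no value). With site in the model the residual variance is (1 − r)σ². Take a pairwise comparison with 80% power unadjusted. The detectable difference is d = (1.960 + 0.842) × √(1/80 + 1/120) = 0.404 SD for 80 v 120 in Part 1, and 2.802 × √(1/100 + 1/100) = 0.396 SD for 100 v 100 in Part 2. In both cases power with site is Φ(2.802/√(1 − r) − 1.960). For r = 0.05 this is Φ(2.874 − 1.960) = Φ(0.914) = 82.0%.

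| r (assumed) | Power with site | CI width ratio √(1 − r) | Equivalent extra patients 1/(1 − r) − 1 |
|---|---|---|---|
| 0 | 80.0% | 1.000 | 0% |
| 0.05 | 82.0% | 0.975 | 5.3% |
| 0.10 | 84.0% | 0.949 | 11.1% |
| 0.20 | 87.9% | 0.894 | 25.0% |

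**4. Check by simulation.** Four-group F test, five sites, site independent of treatment, effects of 0, 0.1, 0.2 and 0.4 SD, 2,500 runs per cell. Power without v with site:

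| r | Part 1 (80/120/80/120) | Part 2 (100 per group) |
|---|---|---|
| 0 | 71.7% v 71.4% | 70.8% v 70.2% |
| 0.05 | 72.3% v 74.5% | 68.6% v 71.1% |
| 0.10 | 72.7% v 76.0% | 70.9% v 74.5% |
| 0.20 | 71.2% v 81.9% | 70.4% v 80.3% |

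With no treatment effect, the rejection rate was about 5% with or without site (range 4.2% to 6.0%; simulation error about 0.4 points). Leaving site out costs precision, not validity, and including it costs almost nothing when sites do not differ.

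**The case against.** The second section's heading covers secondary as well as primary endpoints, and the section on demographics, vital signs and histories applies the tests outlined earlier to those comparisons. One can therefore read the general tests as baseline and descriptive tools, and the efficacy section as governing both endpoint levels. Covariates for each secondary outcome are commonly left to the SAP, which is not shown. No secondary outcome has a power target, so no stated figure fails, and unadjusted comparison in a randomized trial is legitimate.

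Part of this stands. The article does not say that site is to be left out for continuous secondary outcomes. A reader might infer a deliberate omission, but the text supports only an unresolved reading. A reader might also infer that chance imbalance between hospitals biases the arm comparison, since hospital is not a named randomization stratum. It does not: the unadjusted standard error already allows for that imbalance, and type I error stays near 5%.

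What does not stand is that the heading settles the matter. Chi-square and CMH remain stated side by side, and the ANCOVA as written cannot be fitted to outcomes without a baseline. Nor is this merely detail left to the SAP: the article names the tests, and they do not agree.

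**Conclusion.** The concern holds as an inconsistency with a possible loss of precision. Categorical efficacy outcomes have two conflicting tests. For continuous secondary outcomes, the only explicitly stated test has no site term, and the site-adjusted model offered elsewhere names only the primary endpoint.

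The size is modest and uncertain: nothing if sites do not differ, about 2 power points if they carry 5% of the variance, 4 at 10% and 8 at 20%, starting from 80%. These shares are assumptions, so the documents do not support saying that a particular amount of precision is lost. The figures also take study site to mean one of five hospitals, which the article does not define. The primary endpoint's power calculation is not affected.

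**What to change.** - State that the Primary/secondary efficacy endpoints section governs all efficacy endpoints, and that the tests under Statistical analysis serve baseline and descriptive tables.
- Compare continuous secondary outcomes with a linear model containing treatment group and study site, adding surgical site, the randomization stratum, where gastric and colorectal patients are both included (Part 1; Part 2 is colorectal only). Where a preoperative value exists, include it as a covariate.
- Where a rank test is used, make it site-stratified (van Elteren) instead of Kruskal–Wallis.
- Use CMH stratified by site for categorical efficacy outcomes.
- Define study site as hospital or institution.

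Trial status reports Part 1 as already analysed and Part 2 as recruiting. Settle the wording before the Part 2 analysis, and label any such re-analysis of Part 1 as post hoc. The cost is 5 − 1 = 4 degrees of freedom out of about 400 patients per part if site means hospital, and a few lines of code. No new data are needed.

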### Missing data

Missing primary endpoint data will be imputed using the last-observation-carried-forward (LOCF) method. In cases of missing baseline data, the mean of all patients will be used for imputation. Missing data for other observations will not be imputed.

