**Fig. 2 Fig2:**
[figure not shown]
Part 2 study design flowchart. For group details, see Table 2. d days, TEAS transcutaneous electrical acupoint stimulation

Anesthesia protocols will be identical in Part 1 and Part 2 of this study, with midazolam (0.03 mg/kg), propofol (1.5–2.5 mg/kg), sufentanil (0.3–0.4μg/kg), and rocuronium (0.8 mg/kg) used to achieve effective anesthesia, and with patients undergoing mechanical ventilation after tracheal intubation. Anesthesia maintenance during the intraoperative period will be achieved using remifentanil (0.05–0.2 μg/kg/min), propofol, and rocuronium. Sedation depth will be monitored according to the Bispectral Index (BIS), maintaining BIS values between 45 and 55 by adjusting the propofol infusion rate, and adjusting respiratory parameters to maintain a PetCO_2_ of 35-45 mmHg. If a patient’s heart rate (HR) falls below 50 bpm or to 30% below baseline, they will be given 0.25–0.5 mg atropine; if their HR rises to above 100 bpm or to more than 30% above baseline, esmolol (0.2–0.5 mg/kg) will be given as appropriate. If blood pressure falls to < 90/60 mmHg or to below 30% of baseline, 6 mg ephedrine will be administered to maintain hemodynamic stability. Sufentanil (5–10 μg) or 0.05 mg fentanyl will be given as appropriate following peritoneal suturing, and a prophylactic long-acting 5-HT_3_ receptor antagonist will be used. Patients will be connected with a PCIA pump (250 μg sufentanil plus saline to a total volume of 250 ml; 1 ml/h, 3 ml/bolus, 10-min interval). After skin suturing, sedative and analgesic drug administration will be terminated, and patients will be transferred to a post-anesthesia care unit (PACU). After patients resume spontaneous breathing, muscle relaxation antagonists (neostigmine 1–2 mg, atropine 0.5–1 mg, and flumazenil 0.5 mg, if necessary) will be given, and the extubation time will be recorded. Once the patient is fully awake, pain scores will be assessed and adverse events recorded.

GCP-trained nurses will check the bowel sounds by auscultation of the patients’ left lower abdomen or right lower abdomen at 3:00 a.m., 9:00 a.m., 3:00 p.m., and 9:00 p.m. each day on the 1st, 2nd, and 3rd postoperative days. Each auscultation will last for 3 min.

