### Outcome measurement

#### Primary outcome

The primary study outcome will be the time to first bowel sound recovery following surgery, defined as the first time point at which the bowel sounds are heard by GCP-trained nurses at three consecutive time points. The judgment of bowel sounds is based only on the results of auscultation by GCP-trained nurses, even if some patients may feel residual colon gas discharge early after surgery.

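### The auscultation window right-censors any onset after 09:00 on day 3, but the only rule stated for a missing primary endpoint is LOCF, which has nothing to carry for a single event time

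*Protocol article*

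**What the plan says.** Three statements in the protocol article meet here.

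- **Schedule** (Interventions, after Fig. 2): nurses listen "at 3:00 a.m., 9:00 a.m., 3:00 p.m., and 9:00 p.m. each day on the 1st, 2nd, and 3rd postoperative days". No later check is mentioned.
- **Endpoint** (Primary outcome, repeated under Limitations): "the first time point at which the bowel sounds are heard by GCP-trained nurses at three consecutive time points".
- **Missing values** (Missing data): "Missing primary endpoint data will be imputed using the last-observation-carried-forward (LOCF) method".

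The analysis sections name ANCOVA for the primary endpoint, with ANOVA or Kruskal–Wallis as the general between-group tests. None of them mentions censoring or a time-to-event method. Limitations concedes that sounds may be missed between two checks, but does not mention the end of the window.

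**The concern.** The last check is at 21:00 on day 3. An onset dated to 09:00 that day is confirmed by the checks at 15:00 and 21:00; an onset dated to 15:00 or later lacks its second or third confirming check. Slow recoveries are therefore cut off by design, and all that is known of them is that confirmed onset came after 09:00 on day 3.

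LOCF suits a quantity measured repeatedly. Here each patient has one event time or none. If the rule is applied to an unconfirmed patient, either no value results or the time of the last check enters the mean as if recovery had occurred then. A difference in means built on such values does not estimate the difference in mean recovery time on which the trial was sized. The cut-off also falls close to the planning mean of the sham arm, so these patients need not be rare.

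**Working it through.** **Inputs from Sample size calculations.** For sham, "this recovery time was 60.320 ± 9.8167 h in sham TEAS-treated individuals". For TEAS throughout, "51.558 ± 17.8499 h in patients who received TEAS during all phases of the perioperative period". For the effect, "the difference between the two groups was 8.762 h". For the spread, "the larger standard deviation of 17.8 was used to calculate the optimal sample size". The allocation ratio is 3:2 and power is 90%; two-sided α = 0.05 comes from Statistical analysis.

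**Assumptions, not in the article.** Recovery times are normal, and surgery ends at clock hour *e* on day 0, varied from 10:00 to 18:00.

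**1. The plan's own figure.** Smaller arm: n = (1 + 1/1.5) × 17.8² × (1.960 + 1.282)² / 8.762² = 1.667 × 316.84 × 10.507 / 76.77 = 72.3, so 73. Larger arm: 1.5 × 73 = 109.5, so 110. Both match the article, which confirms that the sizing rests on a difference in means of fully observed times.

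**2. Latest confirmable onset.** 09:00 on day 3 lies c = 72 + 9 − e = 81 − e hours after surgery: 71 h if surgery ends at 10:00 and 63 h if it ends at 18:00.

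**3. Share not confirmable.** P(T > c) = 1 − Φ((c − mean)/SD). For example, at 14:00, sham is 1 − Φ((67 − 60.32)/9.8167) = 1 − Φ(0.68) = 24.8%. Pooling uses the 2:3 allocation.

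| Surgery ends | c (h) | Sham | TEAS | Pooled |
|---|---|---|---|---|
| 10:00 | 71 | 13.8% | 13.8% | 13.8% |
| 12:00 | 69 | 18.8% | 16.4% | 17.4% |
| 14:00 | 67 | 24.8% | 19.3% | 21.5% |
| 16:00 | 65 | 31.7% | 22.6% | 26.2% |
| 18:00 | 63 | 39.2% | 26.1% | 31.3% |

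With the planning SD of 17.8 in the sham arm, its share runs from 27.4% to 44.0%. Gamma or lognormal shapes move the pilot-SD figures by about 0 to 4 points.

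**4. Effect on the estimate.** Times were simulated on the 6-hourly grid, with surgery ending uniformly between 11:00 and 19:00 and unconfirmed patients set to 21:00 on day 3.

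- Pilot SDs: a difference of 8.8 h becomes about 9.7 h.
- Both SDs 17.8: 8.7 h becomes about 7.7 h.

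With fixed end times from 10:00 to 18:00, the results run from 9.2 to 10.0 h and from 8.1 to 7.3 h respectively. If 09:00 on day 3 is carried instead, a 14:00 end gives 9.0 h and 5.9 h.

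**5. Type I error (last check carried, 72 vs 108 patients, t-test).** With identical distributions in both arms, rejection is about 5%. With equal means of 56–60 h but SDs of 9.8 and 17.8, a false difference of about 1.2–2.1 h appears and rejection is 6–14%.

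**The case against.** The strongest reply is that the article never says patients unconfirmed on day 3 are missing. The Missing data section may have dropouts in mind, and an unseen analysis plan may classify the unconfirmed. That stands: applying LOCF to them is an inference. It does not rescue the rule, because LOCF has no defined value for a dropout on this endpoint either, and no other rule is stated.

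A reader might also infer more than the article supports:

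- **That a quarter of patients go unconfirmed.** That is one point in a range and depends on an end-of-surgery time the article does not give. If the pilot used the same window, its means and SDs are already truncated and every share is only indicative. The shares need not differ by arm either: at a 10:00 end they are equal.
- **That the primary test loses its type I error.** If TEAS does nothing, both arms have the same distribution and the same window, and a common rule leaves them alike. The 6–14% needs unequal spreads, where TEAS does change the distribution.
- **That the shift is larger.** Dropping unconfirmed patients would give 10.6 h (pilot SDs) or 4.5 h (both 17.8) at a 14:00 end, but the article says impute, not drop.
- **That Part 2 is affected to the same degree.** The article gives no planning means for Part 2, whose patients are all colorectal and all receive TEAS before and during surgery. The structural defect carries over; the figures do not.

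Finally, carrying the last check costs little power: with 73 and 110 patients, both SDs 17.8 and a 14:00 end, it falls from 90% to 89%. The harm is to what the estimate means more than to the chance of a significant result.

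**Conclusion.** The concern holds in this form: the schedule and the endpoint definition together right-censor onsets after 09:00 on day 3, and the one rule stated for absent primary values cannot handle them. This follows from the text alone and needs no assumption.

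The size does need assumptions. With normal times, pilot means and SDs, and surgery ending between 10:00 and 18:00, about 14–31% pooled (14–39% sham, 14–26% TEAS) could not be confirmed. That is above the planned 10% drop-out throughout. If the last check is carried, the mean difference shifts by about 1 h, upward with the pilot SDs and downward with the common planning SD, so no direction of bias can be claimed. Because this concerns the primary comparison and a rule the article states, it should be corrected.

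**What to change.** - Delete LOCF for the primary endpoint.
- Classify patients not confirmed by the last check as right-censored and state the censoring time. 09:00 on day 3 is the last check at which an onset could still be confirmed, which makes it the natural choice. Censor patients lost earlier at their last check, with the same two-check allowance if that convention is adopted.
- Make the primary comparison censoring-aware: for example, a log-rank test stratified by surgical site in Part 1 (the randomisation stratum) and by study site in Part 2. Report Kaplan–Meier medians by group. They should be estimable, since the unconfirmed share stays below one half in every scenario above.
- Apply this prospectively to Part 2, which Trial status describes as still recruiting. Part 1 has been analysed, so report it there as a labelled re-analysis.

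Part 2 needs only wording and code; Part 1 needs one further analysis. The small downside is that the effect is no longer a mean difference. No change to the auscultation schedule is needed, and altering it during Part 2 would make ascertainment differ between patients.

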### Subject disposition

The subject disposition table will be presented for all subjects both overall and arranged according to treatment group. Numbers of study subjects in each population will be summarized, as will numbers who withdraw from the study and their primary reasons for withdrawal.

### Demographic characteristics, vital signs, and medical histories

Demographic characteristics, vital signs, and medical histories for all subjects will be summarized, and between-group comparisons will be conducted as outlined earlier.

### Primary/secondary efficacy endpoints

A covariance model (ANCOVA) will be fitted, with primary endpoint changes from baseline serving as the dependent parameter, and with treatment group, baseline, and study site serving as fixed effects for consideration of site–treatment interactions. For ordinal and categorical variables, a Cochran–Mantel–Haenszel (CMH) test will be used, with study site as a stratifying factor.

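### The primary model analyses change from baseline of a postoperative time that has no baseline value, so it cannot be fitted as written

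*Protocol article*

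**What the plan says.** All places are in the protocol article.

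- **Primary outcome:** "The primary study outcome will be the time to first bowel sound recovery following surgery". The event has to be confirmed, and the time recorded for it is "the first time point at which the bowel sounds are heard by GCP-trained nurses at three consecutive time points".
- **Interventions (text after Fig. 2):** nurses listen four times a day, "each day on the 1st, 2nd, and 3rd postoperative days. Each auscultation will last for 3 min". No preoperative auscultation is described.
- **Primary/secondary efficacy endpoints:** an ANCOVA is fitted "with primary endpoint changes from baseline serving as the dependent parameter". The remaining terms of that model are given separately: "with treatment group, baseline, and study site serving as fixed effects for consideration of site–treatment interactions".
- **Statistical analysis:** "For comparisons between treatment groups", the general rule is that "analyses of variance (ANOVAs) will be used for normally distributed variables", with Kruskal–Wallis otherwise.
- **Sample size calculations:** Part 1 is sized on mean recovery times of 60.320 h (sham) and 51.558 h (TEAS in all phases), with an SD of 17.8 h.
- **Randomization and blinding:** surgical site, gastric or colorectal, is the stratifying factor.
- **Trial status:** Part 1 has completed recruitment and analysis. Part 2 is recruiting.

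**The concern.** A change from baseline needs the same quantity measured before and after treatment. Time to first bowel sound recovery starts running at surgery and is observed once, afterwards. It has no earlier value to subtract and none to adjust for, and the article names no surrogate. The sentence that defines the main efficacy analysis therefore describes a model that cannot be built from the trial's data.

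The analyst must depart from the published text to get any primary result. The departure may be harmless, but if it is not written down in advance, a reader of the results cannot tell whether the model was fixed before or after the data were seen. The stated model also omits the factor on which Part 1 randomization was stratified.

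**Working it through.** **1. Can the model terms be formed?**

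| Term in the stated model | What it needs | What the article provides |
|---|---|---|
| Dependent variable: change from baseline | a value before and after surgery | a postoperative time only |
| Covariate: baseline | a preoperative value | none; auscultation only on days 1 to 3 |
| Treatment group | allocation | available |
| Study site | hospital | available |

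Two of the four terms do not exist for any patient. The rule under Missing data, which replaces a missing baseline by the mean of all patients, does not help: with no observed value there is no mean.

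**2. Which quantity was the trial sized on?** Inputs from Sample size calculations and Statistical analysis: difference 60.320 − 51.558 = 8.762 h; SD 17.8 h; two-sided α = 0.05 (z = 1.960); power 90% (z = 1.282); ratio 3:2, that is 1.5.

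For two independent means of raw time:

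n (smaller group) = (1 + 1/1.5) × (17.8 × (1.960 + 1.282) / 8.762)² = 72.27, rounded up to 73.

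n (larger group) = 1.5 × 73 = 109.5, rounded up to 110.

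Both equal the stated 73 and 110. The sizing is a comparison of raw times with no baseline term. On the same inputs, power is 92.7% with 80 and 120 patients, and 89.9% with the 72 and 108 left after a 10% loss.

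**3. What happens if a constant is forced in as baseline?** A simulated Part 1 data set (80/120/80/120 patients; five sites, assumed from the five hospitals under Design) was given a baseline of 0 h, then 24 h, for everyone. The design matrix has 9 columns (intercept, 3 for group, 4 for site, 1 for baseline) but rank 8, so the baseline coefficient is not estimable. The T3-versus-Con contrast was −5.614 h in both cases, the same as from raw time on group and site. That value comes from simulated data and says nothing about the trial's effect. It shows only that removing the baseline terms loses no information.

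**4. Stratification factor.** Part 1 is stratified by surgical site. The listed fixed effects are treatment group, baseline and study site, so surgical site is absent. Part 2 enrols colorectal patients only, so the term is not needed there.

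**The case against.** The best defence is that this is a slip of template wording. Dropping the baseline terms leaves time on group and site, which agrees with the sizing, does not bias the treatment contrast and costs no power. That is fair on the consequences, but it does not make the printed model correct. The article states a wrong primary analysis, which differs from leaving detail to an analysis plan.

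Three stronger readings are tempting, and the article does not support them.

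- **That the analyst is free to choose among ANCOVA, ANOVA and Kruskal–Wallis.** The general rule under Statistical analysis does not except the primary endpoint. However, the efficacy section has its own heading and names its own methods, and the section on demographic characteristics is the one that refers back to the general rule. The natural reading is that the efficacy section governs. What remains is a need for one clarifying sentence, because the governing model cannot be run.
- **That an interaction in the primary model cuts power.** With equal weighting of five hospitals, variance is multiplied by (1/25) × Σ(1/pᵢ). This is 32.5/25 = 1.30 for shares of 40/20/20/10/10%, and 37/25 = 1.48 for 50/20/10/10/10%. Power of 90% would become about 81% or 76%. The arithmetic is right, but the shares and the equal weighting are assumptions found nowhere in the article. No interaction term is in the list of fixed effects, and the phrase on interactions can equally mean that they will be examined separately.
- **That mean imputation turns baseline into one constant for everyone.** It cannot, because no patient has a value to average.

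**Conclusion.** The point holds. The stated primary model cannot be formed for any patient, since both its dependent variable and its baseline covariate are undefined for this endpoint. It also conflicts with the article's own raw-time sizing and omits the Part 1 stratification factor. This rests on the text alone: the endpoint definition, the auscultation schedule and the model sentence.

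It is an error of specification with no shown numerical harm. The stated 73 and 110 stand, no change in sample size follows, and no loss of power is claimed. It still needs correcting because it concerns the confirmatory analysis, and for Part 2 the correction can still be made in advance.

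**What to change.** Replace the ANCOVA sentence with one primary analysis:

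- **Model:** a linear model of the time itself, in hours from end of surgery to first confirmed bowel sounds, without baseline terms. Treatment group and hospital enter as main effects, plus surgical site (gastric or colorectal) in Part 1.
- **Interaction:** examine site-by-treatment interaction only in a separate secondary model.
- **Precedence:** state that this model is primary for the endpoint, in place of the normality-dependent choice between ANOVA and Kruskal–Wallis. Keep the rank test as a sensitivity analysis.
- **Change from baseline:** keep it for outcomes with a preoperative measurement, such as SF-8 and the immunological and inflammatory indexes.
- **Part 2:** fix this wording before its data are analysed.
- **Part 1:** a new model would now be post hoc. Report which model was actually run and label any departure from the published text.

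No new data or patients are needed. The cost is a protocol amendment, which under Design requires ethics committee approval and an update of the registry entry.
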